## Recruitment

### Screening and consent

Outpatient diabetes surgery appointment clinic lists will be scrutinised ahead of appointments and for people who appear eligible. An information sheet explaining the trial will be sent by post or email as appropriate (including contact details to opt out if the person does not want to be contacted about the trial). Potential participants who are approached have all consented to be contacted to discuss the study further. Before the outpatient appointment, a member of the research team will contact the prospective participant to discuss the study at least 24 h before the outpatient appointment allowing sufficient time for reflection and discussion. This will allow those who are eligible for the study to be randomised immediately after the outpatient appointment. If the participant wishes to take part, they will have the opportunity to discuss the study face-to-face with a research nurse before they give written consent. Final eligibility criteria will be checked before the participant is recruited. Patients whose medical records cannot be accessed prior to the appointment to determine eligibility (e.g. patients from another hospital) will be given information about the study on the day of their outpatient appointment and will be offered the opportunity to come on another day to discuss their participation in the trial. Research nurses at each participating centre will obtain informed consent from trial participants.

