### Randomisation

Once the consent process has been completed, study participants will be randomised into either the intervention group or control group for 12 months. We will randomise on a 1:1 basis using computerised randomisation software. Sealed envelope online software randomisation will be used. Randomisation is blocked and stratified by centre (using random permuted blocks) to ensure groups are balanced.

Those randomised to the intervention group will be asked to complete study questionnaires every three months and the Spotlight Consultation pre-clinic assessment at baseline and follow-up scheduled routine outpatient appointments (Table 1). The results of the Spotlight Consultation digital health assessment will be discussed between the participant and healthcare professional during the outpatient visit along with identified matched care pathways and agreement made on best-fit action plan.

**Table 1 Tab1:** Psychosocial questionnaires

Construct	Measure	Relibaility
Diabetes Distress	DDS [11]	*α*’s=.94
Depression	PHQ-2 [12]	*α*’s=.86
Anxiety	GAD-7 [13]	*r* = 0.782
Engagement	Self-Care Inventory (SCI) [14]	*R*=0.89
Treatment Satisfaction/Utility	Diabetes Treatment Satisfaction Questionnaire [15]	*a* = 0.92
Health Resource Utility	EQ5D [16]	*α*’s=.89
Well-being	WHO-5 [17]	*α*’s=.90
HCP Burnout	Maslach Burnout Inventory [18]	*α*’s=.90

All measures will be administered at baseline, 3, 6, 9 and 12 months

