## The spotlight consultations intervention

### Intervention arm

Participants who are randomised to receive the Spotlight Consultations intervention will be sent a unique secure link to the Spotlight-AQ platform. The platform is commercially available and owned by [name]. The intervention consists of a validated pre-clinic questionnaire that provides insights into individual patient priority concerns across core domains of diabetes management. These priority concerns are presented graphically and form the basis of the discussion within the routine outpatient consultation. Mapped evidence-based resources are available to the HCP to share with their patient based on agreed goals set.

Telemedicine or in clinic visits: Participants will have a telemedicine or in-person clinic visit as per their usual routine care during the trial. Study participants will complete a personal assessment on study tablet devices if face-to-face visit. The support of a research assistant will be available if required. HCPs will also access the results and care pathway options, via their own secure portal logins. HCPs and participants will discuss the priorities and possible options collaboratively in a co-decision making, person-centred approach. Participants will be invited for repeat assessment as per routine care.

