### Control arm

Participants in the control group will continue to receive usual care. Control group participants will be offered access to the Spotlight platform and pre-clinic assessment at the end of the RCT, for use in their next schedule routine outpatient appointment.

Implementing usual care appointments or the outpatient pre-clinic intervention (delivered within one week prior to scheduled routine outpatient appointment) will not change actual treatment for diabetic patients and these will continue for both trial arms.

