### Follow-up

After the participants are randomised to either the intervention or control arm, data will be collected from them at the following timepoints:Pre scheduled routine outpatient appointment (baseline)Three, 6, 9 and 12 months post-randomisation

Participants will be sent reminders to complete follow-up questionnaires a week after they are due, as necessary.

There will be no special criteria for discontinuing or modifying allocated interventions.

Types of data that will be collected from medical records and questionnaire data, in addition to the baseline questionnaires that will be repeated, will be:MortalityAdverse eventsHealth economic questions (adapted CSRI (client survey receipt inventory) questionnaire)

Healthcare professional questionnaire data (Maslach burnout inventory) will be collected at baseline, 6 and 12 months. A sub-group of six k healthcare professionals involved in the delivery of the intervention will be interviewed once around 12 months after the start of the trial in their centre.

The primary outcome data, i.e. length of each consultation, is collected using a stopwatch by participating healthcare professionals and recorded in the study records by the clinical trials team. All other outcome data is electronic and data analysts are not blinded; thus, unblinding will not occur.

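### Follow-up is counted from randomisation but Spotlight waits for a routine appointment, so early questionnaires may precede any exposure; the stated order of randomisation and appointment also conflicts

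*Protocol article*

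**What the plan says.** The article (Recruitment, Screening and consent) describes two ways into the trial.

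- **Main route.** Clinic lists are screened, candidates are contacted at least 24 hours ahead, and those eligible can be "randomised immediately after the outpatient appointment".
- **Late route.** Patients whose records could not be reached in advance learn of the trial on the day of clinic and "will be offered the opportunity to come on another day to discuss their participation in the trial".

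The Randomisation section then applies to everyone: "Once the consent process has been completed, study participants will be randomised into either the intervention group or control group for 12 months". The intervention arm is to complete "the Spotlight Consultation pre-clinic assessment at baseline and follow-up scheduled routine outpatient appointments", and the result is discussed at that visit. The Control arm section says the intervention is "delivered within one week prior to scheduled routine outpatient appointment"; the Abstract agrees. The trial adds no visits of its own: "Participants will have a telemedicine or in-person clinic visit as per their usual routine care during the trial" (Intervention arm).

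The Follow-up section uses two time origins. Baseline is "Pre scheduled routine outpatient appointment (baseline", while the later timepoints are "Three, 6, 9 and 12 months post-randomisation". It also says that the primary outcome, consultation length, is timed by stopwatch at each consultation.

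**The concern.** The follow-up clock starts at randomisation. Exposure starts at a routine appointment whose date the trial does not control. Nothing in the text aligns the two.

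On the late route the appointment that brought the patient in is already over when consent is taken. First exposure is therefore a routine interval away, less whatever time passed before the return day. On the main route, randomising after the appointment has the same effect, and it cannot be squared with a baseline and an intervention that both come before that appointment.

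What is at stake is the set of outcomes read at fixed months: distress, depression, treatment satisfaction, self-care and EQ-5D, and the QALY built from EQ-5D by area under the curve (Health economic analysis). The primary analysis is by intention to treat (Statistics). On that basis, any wave taken before exposure pulls the between-arm difference towards zero.

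**Working it through.** **1. Order of events as written**

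| Step | Late route | Main route, read literally |
|---|---|---|
| Index appointment | already past | just finished |
| Randomisation | when consent is complete | immediately after the appointment |
| Follow-up clock starts | randomisation | randomisation |
| First possible Spotlight | week before the next routine appointment | week before the next routine appointment |

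**2. Which waves precede exposure**

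Let *g* be the months from randomisation to the first routine appointment after it. The article does not give *g*. A wave at month *m* is wholly pre-exposure when *m* < *g*.

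| *g* (assumed) | Waves before exposure |
|---|---|
| up to 3 | none |
| 4 or 6 | month 3 |
| 9 | months 3 and 6 |
| 12 | months 3, 6 and 9 |

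If baseline is taken just before that appointment, as Follow-up implies, then *g* well above 3 would also put baseline after the month 3 questionnaire.

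**3. The plan's own figure**

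Trial design gives 86 per group for a standardised effect of 0.50, alpha 0.05 and 90% power. A two-sided two-sample t test needs 85.03, rounded up to 86, so the figure reproduces. Power is 90.3% with 86 per group and 94.0% with the 100 per group to be recruited.

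**4. Illustrative dilution at one wave**

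Let *f* be the share of participants not yet exposed at that wave, which is also not in the article. With no effect in the unexposed and the standard deviation unchanged, the effect becomes 0.50 × (1 − *f*). The 0.50 is borrowed from the sample size statement, because no effect size is given for any questionnaire.

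| *f* (assumed) | Effect | Power, 86 per group | Power, 100 per group |
|---|---|---|---|
| 0 | 0.500 | 90.3% | 94.0% |
| 5% | 0.475 | 87.2% | 91.7% |
| 10% | 0.450 | 83.5% | 88.6% |
| 20% | 0.400 | 74.2% | 80.4% |
| 30% | 0.350 | 62.6% | 69.2% |

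If the main-route wording were followed literally and every *g* exceeded 3 months, *f* would be 1 at month 3 and the expected difference would be 0.

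**5. Illustrative effect on the QALY**

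Take a lasting utility gain of one unit and apply the trapezoid rule over months 0, 3, 6, 9 and 12.

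- Gain seen from month 3: 1.5 + 3 + 3 + 3 = 10.5 unit-months.
- First Spotlight visit at month 6, gain seen from month 9: 1.5 + 3 = 4.5 unit-months.
- Ratio: 4.5 / 10.5 = 0.43, so such a patient loses 0.57 of the gain.
- Across the trial with a share *f* affected: 0.05 × 0.57 = 3%, 0.10 × 0.57 = 6%, 0.30 × 0.57 = 17%.

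**6. Primary outcome**

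It is recorded at consultations, not at fixed months. The next consultation can be preceded by Spotlight, so the dilution in step 4 does not apply to it. It is missing only for a patient with no appointment within follow-up.

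**The case against.** The strongest case against the point has four parts.

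- **The interval is unknown.** With the next appointment within 3 months, no wave is wholly pre-exposure, and the return day might fall shortly before that appointment. This stands. A reader might infer that early outcomes are taken before exposure as a matter of course, but the article supports only that they may be.
- **An article condenses the full protocol, and the late route looks exceptional.** Scheduling detail could well be left out. But the point does not rest on missing detail. The stated rules for randomisation, follow-up and delivery produce the misalignment, and the main-route conflict is on the page.
- **The intended sequence seems clear.** Spotlight is given at baseline and baseline precedes an appointment, so the authors probably meant the three to go together. That is a fair reading, but follow-up is still counted from randomisation and the main-route sentence still places randomisation after the appointment.
- **The power figures borrow the primary outcome's effect size.** The trial calls itself exploratory and claims no power for the questionnaires. With 100 per group, 10% unexposed still leaves 88.6%. This stands, and the figures show scale only.

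A reader might also infer that the primary comparison loses power, or that the primary outcome is generally lost. The documents support neither, for the reason in step 6 of the working.

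**Conclusion.** The point holds in conditional form. The article's own rules let follow-up start before exposure can, certainly on the late route and, read literally, on the main route too. The main-route sentence also contradicts the Randomisation, Control arm and Follow-up sections.

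Whether any wave is wholly pre-exposure depends on an unstated appointment interval of more than 3 months for month 3, more than 6 for month 6 and more than 9 for month 9. The size of the dilution cannot be computed from the article, since neither the interval nor the share on the late route is given. Under the assumed shares of 5% to 30%, a month 3 effect of 0.50 would fall to between 0.475 and 0.35.

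The damage is confined to secondary questionnaire outcomes and the QALY. This is a cheap improvement to the plan, not a threat to the primary comparison.

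**What to change.** Reconcile Screening and consent, Randomisation, Control arm and Follow-up on a single order of events:

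1. On both routes, randomise before the first study appointment. For late-route patients that is their next scheduled routine appointment.
2. In both arms, date baseline and the month 3, 6, 9 and 12 follow-up from the scheduled date of that appointment. Fix the date before allocation, so that the arm cannot influence the time origin.
3. Where the schedule and the recruitment window allow, randomise shortly before that appointment, but do not make this a condition of enrolment.

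The last clause matters. Recruitment runs from 18 October 2021 to 31 March 2022, which is 164 days. If randomisation had to wait for the week before the next appointment, a 6-month interval (about 182 days) would allow it no earlier than day 182 − 7 = 175, after recruitment closes, and nobody on the late route could enter. At about 92 days, only patients informed in the first 164 − 85 = 79 days could enter, about half. Moving the time origin alone excludes nobody on these grounds and keeps the intention-to-treat comparison.

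The cost is a few sentences, plus somewhat longer calendar follow-up and possible dropout between randomisation and the first appointment for late-route patients.

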### Randomisation

Once the consent process has been completed, study participants will be randomised into either the intervention group or control group for 12 months. We will randomise on a 1:1 basis using computerised randomisation software. Sealed envelope online software randomisation will be used. Randomisation is blocked and stratified by centre (using random permuted blocks) to ensure groups are balanced.

Those randomised to the intervention group will be asked to complete study questionnaires every three months and the Spotlight Consultation pre-clinic assessment at baseline and follow-up scheduled routine outpatient appointments (Table 1). The results of the Spotlight Consultation digital health assessment will be discussed between the participant and healthcare professional during the outpatient visit along with identified matched care pathways and agreement made on best-fit action plan.

**Table 1 Tab1:** Psychosocial questionnaires

Construct	Measure	Relibaility
Diabetes Distress	DDS [11]	*α*’s=.94
Depression	PHQ-2 [12]	*α*’s=.86
Anxiety	GAD-7 [13]	*r* = 0.782
Engagement	Self-Care Inventory (SCI) [14]	*R*=0.89
Treatment Satisfaction/Utility	Diabetes Treatment Satisfaction Questionnaire [15]	*a* = 0.92
Health Resource Utility	EQ5D [16]	*α*’s=.89
Well-being	WHO-5 [17]	*α*’s=.90
HCP Burnout	Maslach Burnout Inventory [18]	*α*’s=.90

All measures will be administered at baseline, 3, 6, 9 and 12 months

### Outcome measures

Primary outcome measure: duration of routine outpatient consultation.

Secondary outcome measures:Functional health status (EQ5D)Diabetes distressDepressionTreatment satisfactionImpact on self-care behaviours (Self-Care Inventory)HCP burnoutHCP treatment satisfaction and burdenHypoglycaemia (time less than 70mg/dL) (for those participants using CGM as standard care)Hyperglycaemia (time above 180 mg/dL) (for those participants using CGM as standard care)Change in weightChange in HbA_1c_Cost effectiveness of intervention (adapted CSRI and bespoke measures)

## The spotlight consultations intervention

### Intervention arm

Participants who are randomised to receive the Spotlight Consultations intervention will be sent a unique secure link to the Spotlight-AQ platform. The platform is commercially available and owned by [name]. The intervention consists of a validated pre-clinic questionnaire that provides insights into individual patient priority concerns across core domains of diabetes management. These priority concerns are presented graphically and form the basis of the discussion within the routine outpatient consultation. Mapped evidence-based resources are available to the HCP to share with their patient based on agreed goals set.

Telemedicine or in clinic visits: Participants will have a telemedicine or in-person clinic visit as per their usual routine care during the trial. Study participants will complete a personal assessment on study tablet devices if face-to-face visit. The support of a research assistant will be available if required. HCPs will also access the results and care pathway options, via their own secure portal logins. HCPs and participants will discuss the priorities and possible options collaboratively in a co-decision making, person-centred approach. Participants will be invited for repeat assessment as per routine care.

### Control arm

Participants in the control group will continue to receive usual care. Control group participants will be offered access to the Spotlight platform and pre-clinic assessment at the end of the RCT, for use in their next schedule routine outpatient appointment.

Implementing usual care appointments or the outpatient pre-clinic intervention (delivered within one week prior to scheduled routine outpatient appointment) will not change actual treatment for diabetic patients and these will continue for both trial arms.

### Follow-up

After the participants are randomised to either the intervention or control arm, data will be collected from them at the following timepoints:Pre scheduled routine outpatient appointment (baseline)Three, 6, 9 and 12 months post-randomisation

Participants will be sent reminders to complete follow-up questionnaires a week after they are due, as necessary.

There will be no special criteria for discontinuing or modifying allocated interventions.

Types of data that will be collected from medical records and questionnaire data, in addition to the baseline questionnaires that will be repeated, will be:MortalityAdverse eventsHealth economic questions (adapted CSRI (client survey receipt inventory) questionnaire)

Healthcare professional questionnaire data (Maslach burnout inventory) will be collected at baseline, 6 and 12 months. A sub-group of six k healthcare professionals involved in the delivery of the intervention will be interviewed once around 12 months after the start of the trial in their centre.

The primary outcome data, i.e. length of each consultation, is collected using a stopwatch by participating healthcare professionals and recorded in the study records by the clinical trials team. All other outcome data is electronic and data analysts are not blinded; thus, unblinding will not occur.

### Qualitative evaluation

The aims of the qualitative evaluation are to understand and explore:Participants’ experiences, including gender-specific experiences, of receiving Spotlight Consultations tool and health professionals’ views about delivering itThe perceived benefits of Spotlight Consultations from participants’ and health professionals’ perspectives, and their recommendations for future refinementsAny changes participants make to their diabetes self-management practices and treatment goals after receiving Spotlight Consultations intervention and whyWhether, in what ways and why, Spotlight Consultations is delivered and received differently in different settingsWhether there are any site-specific differences in how participants self-manage their diabetes after receiving Spotlight Consultations, and why

#### Participant interviews

Twenty participants randomised to receive the intervention will be interviewed 6 months following their visit to explore whether, how and why, their diabetes self-management practices and treatment goals have changed in the intervening period, and any perceived barriers to achieving future changes and goals. These interviews will explore their experiences of receiving Spotlight Consultations tool; any changes made to their diabetes self-management practices, and why; short- and long-term treatment goals and the reasons for these; and perceived barriers and facilitators to achieving these goals. These interviews will also include detailed exploration of participants’ historical diabetes management practices; previous contact with health professionals and diabetes management programs; and their everyday work and family lives. The interviews will also explore participants’ information and support needs and whether, and in what ways, the intervention and follow-up care could be changed or improved. Purposive sampling strategies will be employed to ensure representation across age, duration of diabetes, type of diabetes/pre-diabetes, presence of complications and therapy. Consent will be taken as part of the overall informed consenting process.

#### Health professional interviews

Six health professionals involved in Spotlight Consultations delivery will be interviewed once at the end of the trial. Interviews will explore the following: previous experiences of delivering self-management interventions for adults with diabetes; perceived benefits of Spotlight Consultations as compared to other interventions; experiences of, and views about, the training received to deliver Spotlight Consultations; barriers and facilitators to intervention delivery; perceived impact of Spotlight Consultations on participants’ diabetes self-management practices; and how Spotlight Consultations could be changed/improved for future use. Consent will be taken as part of the overall informed consenting process. One healthcare professional will be randomly selected from each centre.

##### Qual topic guides

Participant and health professional interviews will be informed by topic guides, with questioning kept sufficiently flexible to enable individual issues to be identified and explored. Semi-structured interviews will be used with a combination of closed and open questions. All interviews will be audio-recorded, transcribed in full, and early interviews will be reviewed by the research team to determine whether any alterations to the topic guides need to be made.

